**Research Purpose**

The main purpose of this pilot study is to determine whether RIPC affects measures of exercise capacity in patients with non-ischemic left ventricular dysfunction and symptomatic heart failure. Differential effects on various exercise performance measures could also provide mechanistic insights into the benefits seen with RIPC.

A secondary aim of the study is to determine whether the protective humoral factor, known to be released into the bloodstream of healthy individuals during RIPC, is similarly released by patients with heart failure. This will require a sub-study of the effect of dialysed patient plasma on explanted mice hearts in a Langendorff preparation. Any protective effects of RIPC in our Langendorff heart model will be correlated with exercise performance in heart failure patients.

If we find that RIPC is associated with improvements in cardiac and skeletal muscle function and exercise capacity in this study, we plan on conducting a larger randomized controlled trial to assess the therapeutic effects RIPC on clinical outcomes in a broader spectrum of heart failure patients.

Study participants would include patients followed in the Heart Function Clinic at the Toronto General Hospital, a referral center for heart failure management and cardiac transplantation evaluation. This multidisciplinary clinic actively follows approximately 850 patients and sees 25-30 new referrals per month. Clinic patients undergo routine assessment, including cardiopulmonary exercise testing by a trained exercise physiologist at regular intervals as dictated by clinical circumstances. In general, the target population has a baseline risk of death in excess of 30% per year and would be expected to have at least a moderate impairment in exercise capacity. Consequently, Heart Function Clinic patients represent an ideal sample population in which to study the effects of RIPC on exercise performance.

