**Methods**

*Study Design*

This pilot study will be a randomized double blind cross-over trial of RIPC in ambulatory heart failure patients undergoing cardiopulmonary stress testing. One-half of study patients will be randomly assigned to RIPC treatment in the first session, and the second half of the patients will receive sham preconditioning prior to exercise testing. The following week, patients will undergo whichever protocol they had not completed in the first session, prior to repeat exercise testing. In this manner, patients will be exposed to both the RIPC and sham treatments.

Investigators and patients will be blinded to treatment allocation. The specific RIPC intervention will include four 5-minute cycles of upper limb blood pressure cuff inflation to 20mmHg above systolic blood pressure to induce forearm ischemia. Each 5-minute cycle of ischemia will be followed by 5 minutes of reperfusion (blood pressure cuff fully deflated). The sham-control arm similarly will include four 5-minute cycles of blood pressure cuff inflation to 10mmHg only, interspersed with 5 minutes of cuff deflation. Following blood sampling (see below), the, patients will then perform a routine cardiopulmonary exercise test under the supervision of a single dedicated exercise physiologist who will be blinded to treatment assignment.

The cardiopulmonary exercise study consists of a standard stationary bicycle ramp protocol in which workload increases by 10 watts per minute. The study is symptom- limited once a target respiratory exchange ratio (RER) of  1.05 is achieved. The RER  1.05 indicates that the patient has exercised with sufficient intensity to induce lactic acidosis as a byproduct of anaerobic metabolism. The exercise study would also terminated prematurely for any of the following: hypotensive response ( 10mmHg drop in systolic blood pressure) to increasing work load, lightheadedness, signs of poor perfusion, signs of significant ischemia on the ECG ( 2mm horizontal/downsloping ST segment depression or  1mm ST segment elevation in non-infarct leads), significant brady or tachyarrhythmia including ventricular tachycardia, hypertensive response to exercise (systolic blood pressure ≥250 mmHg or diastolic blood pressure  110mmHg) or upon patient request.

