# Study Endpoints

Clinical endpoints will be ascertained at the conclusion of the cardiopulmonary stress test. The primary endpoint will be peak VO2 in patients achieving a respiratory exchange ratio >1.05. Secondary endpoints include other measures of exercise performance: ventilatory threshold, peak VE/VCO2 slope, workload achieved in Watts, total exercise time and oxygen uptake efficiency slope. We will also assess serum lactate post stress to directly determine the effect of RIPC on lactic acid production under anaerobic conditions.

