# Sample Size and Data Analysis

This pilot study will be conducted with a sample size of 44 patients to determine baseline exercise parameter and variance values in our study population. Assuming that our patients are similar to contemporary heart failure patients evaluated in exercise training trials, mean baseline exercise peak VO2 is expected to be approximately 14.0 –15.0 mL/kg/min, with an estimated standard deviation of 2.5 mL/kg/min. A 44 patient cross-over trial would therefore provide 80% power to detect a difference of 1.5 mL/kg/min, which represents a clinically significant ~10% change in peak VO2 (2-tailed alpha level 0.05).

Continuous variables will be summarized using means and standard deviations and contiguous variables will be summarized as proportions. Student’s T test and chi squares will be used to determine differences between continuous and categorical variables, respectively. Pre-specified subgroup analyses will assess the effect of RIPC on patients with moderately severe exercise limitation (sham peak VO2 <14mL/kg/min) or very severe exercise limitation (sham peak VO2 <10mL/kg/min), as well as its effect on patients taking beta blockers versus those not taking beta blockers.

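### The severity subgroups are selected on sham peak VO2, which is also the comparator in the treatment difference, so the subgroup below 14 mL/kg/min is expected to show a RIPC benefit even if there is none

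*Protocol*

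**What the plan says.** Under Methods (Study Design), every patient has one exercise test after RIPC and one after sham, a week apart in random order: "patients will be exposed to both the RIPC and sham treatments". Under Study Endpoints, "The primary endpoint will be peak VO2 in patients achieving a respiratory exchange ratio >1.05".

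Sample Size and Data Analysis then fixes the severity subgroups: the effect of RIPC will be assessed in "patients with moderately severe exercise limitation (sham peak VO2 <14mL/kg/min) or very severe exercise limitation (sham peak VO2 <10mL/kg/min"). These analyses are labelled pre-specified. The same section gives the planning values used below: "mean baseline exercise peak VO2 is expected to be approximately 14.0 –15.0 mL/kg/min", "with an estimated standard deviation of 2.5 mL/kg/min" and "This pilot study will be conducted with a sample size of 44 patients".

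The baseline variables listed under Study Patients include no peak VO2 measured before the study sessions. Research Purpose says that clinic patients have routine assessment, "including cardiopulmonary exercise testing by a trained exercise physiologist at regular intervals as dictated by clinical circumstances".

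**The concern.** A single exercise test measures a patient's capacity with error. A patient can fall below 14 on the sham day because capacity is truly low, or because that day's test was poor. Selecting on a low sham value collects both kinds. On the RIPC day the chance part is not expected to recur, so the RIPC-minus-sham difference is pushed upward in the selected group. This is regression to the mean. Neither randomised order nor blinding removes it, because the selection uses one half of the difference itself.

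The sham value is also not a baseline. It is measured after randomisation and, for about half the patients, after they have already received RIPC.

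At stake is the reading of a pre-specified result. An apparent benefit in the more limited patients would carry the credibility of advance planning, although the definition favours that finding when RIPC does nothing.

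**Working it through.** **Inputs.** From Sample Size and Data Analysis: 44 patients, SD 2.5, mean 14.0 to 15.0 (midpoint 14.5), target difference 1.5, two-sided alpha 0.05, cut-offs 14 and 10. Assumed, because the protocol does not give it: test-retest correlation ρ of 0.7 to 0.95. Also assumed: normal values with equal SD in both sessions, all 44 patients evaluable, and a paired t test within the subgroup (the protocol names a t test without saying paired or unpaired).

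**The plan's own figure.** 2 × (1.960 + 0.842)² × 2.5² / 1.5² = 43.6, so 44, which matches the stated 80% power. As a paired calculation this uses an SD of differences of 2.5 × √2 = 3.54, that is, ρ = 0. The sample size therefore gives no usable estimate of repeatability.

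**Formula with no RIPC effect.** For cut-off c, with z = (c − mean)/SD, φ the standard normal density and Φ the distribution function:

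expected (RIPC − sham), given sham < c, = (1 − ρ) × SD × φ(z)/Φ(z).

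**Cut-off 14, mean 14.5.** z = −0.5/2.5 = −0.2; φ = 0.3910; Φ = 0.4207. The expected subgroup size is 44 × 0.4207 = 18.5. SD × φ/Φ = 2.5 × 0.3910/0.4207 = 2.32, which is multiplied by (1 − ρ). False-benefit rates come from 20,000 simulated null trials of 44 patients per setting, counting results significant in favour of RIPC (nominal 2.5%).

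| ρ (assumed) | Spurious benefit, mean 14.5 | Range, mean 14.0 to 15.0 | False benefit, mean 14.5 | Range, mean 14.0 to 15.0 |
|---|---|---|---|---|
| 0.7 | +0.70 | 0.60 to 0.80 | 34% | 31 to 36% |
| 0.8 | +0.46 | 0.40 to 0.53 | 24% | 21 to 25% |
| 0.9 | +0.23 | 0.20 to 0.27 | 14% | 13 to 14% |
| 0.95 | +0.12 | 0.10 to 0.13 | 9% | 8 to 9% |

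**Cut-off 10, mean 14.5.** z = −4.5/2.5 = −1.8; φ = 0.0790; Φ = 0.0359. SD × φ/Φ = 5.49, so the spurious benefit is +1.65, +1.10, +0.55 and +0.27 at the same four correlations. The expected size is 44 × 0.0359 = 1.6 patients (2.4 at mean 14.0, 1.0 at mean 15.0). At mean 14.5 the binomial chance of 0 or 1 such patient is 53%, in which case no t test is possible.

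**Check of the two-session mean as classifier.** The covariance of (RIPC + sham)/2 with (RIPC − sham) is half the difference of the two variances. It is zero when the variances are equal, and simulation then gives no bias below 14 and a two-sided type I error of 4.8 to 5.4%. Suppose instead that individual response to RIPC averages zero, is unrelated to severity, and varies with SD τ. The RIPC variance becomes 6.25 + τ² and the covariance τ²/2. For τ = 1.0 and ρ = 0.8, the variance of the mean is (6.25 + 7.25 + 2 × 5)/4 = 5.875, with SD 2.42. Then z = −0.5/2.42 = −0.206 and φ/Φ = 0.934, so the bias is −(0.5/2.42) × 0.934 = −0.19. For τ = 1.5 and ρ = 0.8 the same steps give −0.42. This classifier can therefore show spurious harm of about 0.2 to 0.4 mL/kg/min.

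**The case against.** The best case against is one of proportion. The trial calls itself a pilot, and this is a supporting analysis. The comparison of RIPC with sham in the full sample does not use the classifier, and neither does the beta-blocker subgroup. The size rests on a correlation that the protocol does not state, and at 0.95 the bias is only about 0.12 mL/kg/min. All of this stands. It limits the weight of the point, but not its direction, which is upward for any correlation below 1. Nor can the point be left to a statistical analysis plan that is not shown, because the protocol itself fixes the classifier.

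Some stronger readings are tempting and are not supported:

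- A reader might infer that the subgroup result would choose the population of the larger trial. Research Purpose makes that trial depend on a favourable finding and foresees a wider range of heart failure patients, not a narrower one. Neither statement under Hypothesis says that sicker patients benefit more.
- A reader might add apparent harm in patients at or above 14 and a false difference between groups. The arithmetic would produce both, but the protocol defines no such group and plans no such contrast; it sets two groups against each other only for beta blockers.
- A reader might stress that the bias below 10 reaches the 1.5 target. Within the assumed range and at mean 14.5 it does so only at correlation 0.7, in one or two patients.
- A reader might insert the zero correlation implied by the sample size, which would put the artefact below 14 at 2.3, above the target. That zero is a by-product of the formula used; the protocol does not claim that repeat tests are unrelated.

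**Conclusion.** The point holds as a real flaw in a supporting analysis. As defined, the subgroup below 14 is expected to show a RIPC benefit of about 0.1 to 0.7 mL/kg/min with no true effect, at mean 14.5 and assumed correlations from 0.95 down to 0.7. A significant false benefit occurs about three to fourteen times as often as the nominal 2.5%. The direction is certain for any correlation below 1. The size depends on the assumed correlation, on normality and on equal SDs, and the error rates depend also on a paired t test. The group below 10 shares the bias but is too small to support any inference. The trial's main conclusion is not threatened.

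**What to change.** In Sample Size and Data Analysis, replace sham peak VO2 as the classifier with the most recent clinical peak VO2 obtained before the first study session, where available. Its error is not shared with either study test, so it does not build in a difference between them. The cost is one sentence and a chart extraction. The value is not on the baseline list under Study Patients, and clinic testing follows clinical need, so it may be missing or old for some patients; the text should say so.

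Where no such value exists, use the mean of the patient's two session values as a sensitivity classifier. State that it is also measured after randomisation, is unbiased only if the RIPC and sham variances are equal, and can show spurious harm if response to RIPC varies between patients. It needs no new data.

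Report the group below 10 descriptively, without a test. Make the change before unblinding.

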# Sub-study Design

*i) Preparation of plasma dialysate:*

25 of blood will be taken after the RIPC or sham RIPC protocol has been completed. Each sample will be anonymised and coded according to treatment assignment, stored on ice and transferred to the [name] laboratory in the MacMaster building, Sickkids. Subsequently, the plasma fraction will be separated by centrifugation (3,000 *g* for 20 min). To prepare dialysate, 12-15 of plasma will be placed in dialysis tubing with a 12-14 kDa cut-off membrane (Spectrapor, USA), dialysed against a 20 fold volume of Krebs buffer (240-300 mL) while stirred overnight at 4oC, and stored at -80oC**.** Prior to perfusion of the mouse hearts, D-glucose, NaHCO3 and EDTA are added to a final concentration of 15mM, 25 mM and 0.5mM, respectively to the dialysate.

*ii) Mouse langendorff:*

After a 20-min stabilization period, isolated hearts will be perfused for 30 min using dialysate, then washed out for 5min, and then subjected to 30 min of no-flow global ischemia followed by 60min of reperfusion. HHeHemodynamic measurements, including heart rate (HR), peak left ventricular pressure (LVP), maximum rate of contraction (+dP/dtmax), maximum rate of relaxation (-dP/dtmin), and LVEDP will be recorded on a data acquisition system (PowerLab, ADInstruments) throughout the procedure. Coronary flow rate will be calculated by measuring the amount of effluent emerging from the heart per minute (ml/min). Myocardial infarction size will be measured in heart slices stained with 1.25% triphenyltetrazolium chloride (TTC) in 200mM Tris pH 7.4 for 15 min in 37oC water bath. Afterfixation for 4-6 hours in 10% neutral buffered formaldehyde, both sides of each slice will photographed by electronic scanning (CanoScan 4400F) and the infarct area measured by automated planimetry using Adobe Photoshop® CS2 software. All personnel involved in the preparation and assessment will be blinded to treatment assignment.

# **Specific Patient Risks**

# Exercise Testing

Patients with advanced heart failure routinely undergo cardiopulmonary stress testing for diagnostic and prognostic purposes. Exercise testing is considered safe in the broad spectrum of patients being evaluated for cardiac disease, with a risk of death or non-fatal myocardial infarction estimated at 1/2500. Patients are electrocardiographically monitored, and symptoms, heart rate and blood pressure are assessed at regular intervals throughout the test.

In the heart failure population, a large proportion of patients have implantable cardioverter defibrillators (ICDs). There is a theoretical risk of receiving a shock during exercise, however ICDs are not considered a contraindication to stress testing provided patients are supervised, and that exercise heart rate does not exceed the arrhythmia detection threshold rate. In our practice, patients with ICDs are carefully supervised to ensure they do not approach their set arrhythmia detection rate, with a typical margin of safety of 10 beats per minute.

Ischemic preconditioning with blood pressure cuff induced skeletal muscle ischemia may result in brief local discomfort, a tingling sensation or transient muscle weakness in the affected arm. There are no known longer-term risks associated with this intervention.

# Blood sampling

Blood draws for laboratory measurements may be associated with discomfort and/or bruising and the possibility of infection. To minimize risks, puncture sites will be disinfected with alcohol swabs and a band-aid applied for hemostasis. All materials used in blood punctures will be used once and discarded into a biohazard waste container.

# **Anonymity and Confidentiality**

Participating patients will be assigned a unique identifying code to preserve anonymity. Data will be collected and maintained by the investigators only, and all paper and electronic records will be kept in a secure location at the Toronto General Hospital.

# **Compensation**

Patients will be reimbursed for parking costs but will receive no other compensation for their participation in this study.

# **Informed Consent**

Information will be provided to participants in a manner that is understandable to them. All aspects of the project including rationale and procedures involved will be carefully explained. Patients will understand that their participation in this study is completely voluntary and that they are free to withdraw at any time without repercussion. A decision not to participate will in no way affect their care through the Heart Function Clinic. Participating patients will receive a copy of the letter explaining the study as well as the signed consent form.
